### Analysis of results

The data collected will be analyzed by using the statistical software Statistical Package for Social Sciences (SPSS) and checked for normality via Kolmogorov-Smirnov analysis. All data will be normally distributed as indicated by *p*>0.05 unless otherwise stated. If the data will be not normally distributed, analyses will be carried out on the natural logarithm of the values to improve the symmetry and homoscedasticity of the distribution.

Descriptive statistics, including percentages, mean values, and standard deviations, will be used to describe the baseline demographic data, type of diseases, nutritional status level including anthropometric data, and dietary intake. The median will be used when the data are skewed. When the data become skewed, the mean loses its ability to provide the best central location for the data because the skewed data are dragging it away from the typical values. In addition, the median is not strongly influenced by skewed values.

The values from both groups will be compared using an ANOVA test for approximately normally distributed data, followed by tests on pairs of groups using the Bonferroni adjustment. Non-normal data will be compared by the Kruskal-Wallis test followed by the Mann-Whitney *U* test. ANCOVA or logistic regression will be used with models adjusted according to potential confounders to determine predictors of changes in the key outcome variables of the length of hospital stay with *p*<0.05 significance level. An intent-to-treat (ITT) analysis will be performed to determine the effect of the intervention study on the assumption that participants have adhered to the dietary advice and ONS at the start of the intervention study and had baseline and endpoint values. In other words, ITT analysis includes every randomized subject; according to randomized treatment assignment regardless of their non-compliance, subsequent withdrawal from treatment, or deviation from the protocol and anything that happens after randomization. The effect of intervention between treatment groups on outcome parameters will be carried out by using General Linear Model (GLM) for repeated measure procedure. This method is quite robust to violation of the assumption of normality [33].

A partial Eta-squared measure will be used to compare the magnitude of changes with the large effect size, indicating a significant difference in magnitude [34]. Using Cohen’s classification, the value of partial Eta-squared is considered to be a small effect size at 0.01, a moderate effect size at 0.06, and a large effect size at 0.14 [35].

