**Methods:**

This is a pragmatic randomized control trial study where elective admitted patients will be randomly divided into the intervention (SS) or control (NN) group. All data will be collected during a face-to-face interview, anthropometric measurement, blood sampling (albumin, white blood count, hemoglobin, and c-reactive protein), handgrip strength, and postoperative complications. Group SS will be receiving a tailored lifestyle and intensively supplemented with oral nutrition support as compared to Group NN that will receive standard medical care. The primary outcome *for this study is* the length of stay in the hospital. Additional outcome measures are changes in biochemical profile and nutritional and functional status. The effects of intervention between groups on the outcome parameters will be analyzed by using the SPSS General Linear Model (GLM) for the repeated measure procedure.

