**Complications postoperative**				
Length of stay in hospital			/	

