### Primary outcome measure

#### Length of hospital stay

Length of hospital stay will be recorded starting from postoperative day 1 until the day of the patient’s discharge. The total length of hospital stay will be taken during visit 2, the day of the patient’s discharge.

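### No single workable primary analysis is fixed for length of stay: the named model cannot be run on it, a normality test chooses between the others, and the non-normal route has two conflicting rules

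*Protocol article*

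**What the plan says.** The Protocol article makes length of stay the primary outcome and defines one value per patient: "Length of hospital stay will be recorded starting from postoperative day 1 until the day of the patient’s discharge". In Table 3 the row "Length of stay in hospital" is marked at visit 2 only, and Data collection procedure agrees that the value is available only then.

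Four statements then bear on its analysis.

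- **Normality gate (Analysis of results).** Data are "checked for normality via Kolmogorov-Smirnov analysis", with the reading "All data will be normally distributed as indicated by *p*>0.05 unless otherwise stated". The normal route is: "The values from both groups will be compared using an ANOVA test for approximately normally distributed data".
- **Non-normal route (same section).** One paragraph says: "If the data will be not normally distributed, analyses will be carried out on the natural logarithm of the values". A later one says: "Non-normal data will be compared by the Kruskal-Wallis test followed by the Mann-Whitney".
- **Intervention effect.** According to the abstract, effects between groups on the outcome parameters "will be analyzed by using the SPSS General Linear Model (GLM) for the repeated measure procedure". Analysis of results repeats this and adds that the procedure is robust to non-normality.
- **The one analysis sentence that names length of stay.** It offers ANCOVA or logistic regression, adjusted for potential confounders, to find predictors.

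Sample size calculation rests on a 3.45-day difference between groups and a standardised effect of 0.8.

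**The concern.** None of these statements, alone or together, tells an analyst which test and which effect estimate answer the primary question.

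The repeated-measures model needs several values per patient, and length of stay has one. The normality gate covers all data with no exception for the primary outcome, so on the natural reading it decides between ANOVA and something else. A non-significant normality test with about 30 patients per arm is weak evidence of normality, and once data are declared non-normal the article points two ways. The ANCOVA or logistic choice is a further open option. Logistic regression would need a cut-point in days, and none is given.

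At stake is the meaning of the primary result. ANOVA estimates a difference in mean days, the log analysis a ratio of geometric means, and the rank test a shift in ranks. Only the first is on the scale used to size the trial.

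**Working it through.** **1. The plan's sample size.** Inputs from Sample size calculation: d = 0.8, power 90%, alpha 0.05 (sidedness not stated), dropout 20%, 34 per group.

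- Two-sided: n = 2(1.960 + 1.282)²/0.8² = 32.8, so 33 per arm. The exact t version is 33.8, so 34 per arm, before any dropout allowance.
- One-sided: n = 2(1.645 + 1.282)²/0.8² = 26.8, so 27 per arm, and 27/0.8 = 33.75, so 34.

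The stated 34 reproduces either way, and both calculations are for a difference in means. If the two planning figures belong together, the implied SD is 3.45/0.8 = 4.31 days.

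**2. Which statements can apply to length of stay?**

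| Analysis named | Usable for one value per patient? | Estimates |
|---|---|---|
| Repeated-measures GLM | No | – |
| ANOVA, if K-S p>0.05 | Yes | Difference in mean days |
| Analysis of ln(values), if not normal | Yes | Ratio of geometric means |
| Kruskal-Wallis / Mann-Whitney, if not normal | Yes | Rank shift |
| ANCOVA | Yes | Adjusted difference in mean days |
| Logistic regression | Only after a dichotomy that is not defined | Odds ratio |

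**3. How often would the choice matter?** The article gives no mean, SD or shape for length of stay, so these are assumptions:

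- log-normal stays rounded to whole days, minimum 1;
- control mean 10, intervention mean 10 − 3.45 = 6.55, with the same coefficient of variation;
- control SD 4.31 (plan-implied), 6 or 8;
- log-scale variance ln(1 + CV²), log-scale mean ln(mean) minus half that variance;
- 34 per arm and two-sided 0.05.

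Ranges cover repeated simulations of 2,000 to 4,000 trials per setting.

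| Control SD | Power: days | Power: ln(days) | Power: Mann-Whitney | Tests disagree |
|---|---|---|---|---|
| 4.31 | 98% | 99% | 98–99% | about 2% |
| 6 | 81–83% | 87–88% | 85–87% | 10–12% |
| 8 | 58–60% | 68–69% | 65–66% | 18–20% |

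Power at SD 4.31 exceeds the planned 90% because a proportional reduction also shrinks the intervention SD, to 6.55 × 0.431 = 2.82. With 27 per arm (34 × 0.8 = 27.2), disagreement is about 4% at SD 4.31 and 13–14% at SD 6.

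**4. What decides the branch?** At SD 6 and 34 per arm, K-S is non-significant in both arms in about 73–79% of trials if uncorrected for the estimated mean and SD, and in about 5–7% if corrected. The article does not say which version is meant, or whether the check is per arm or pooled.

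**5. Error rate with no effect.** Following the two-stage rule mechanically, with either non-normal rule, gives a type I error of about 4.5–5.7%. At least one of the three tests is significant in about 7%.

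**The case against.** **The gate is written in advance and holds the error rate.** This stands. A reader might infer that the pre-test inflates type I error. It does not when followed as written. The figure of about 7% arises only if whichever test is significant is reported. The article does not propose that, although two competing non-normal rules leave room for it.

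**The gate does not name length of stay.** True: its application to the primary outcome is an inference from wording that covers all data. But the only other sentence naming that outcome leaves its own choice open, so this does not supply a fixed test.

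**When skew is missed, the weaker test is used.** A reader might infer this from the power table, which averages over all trials. Among trials at SD 6 where both arms pass the uncorrected K-S, ANOVA has 84% power against 87% for the log analysis. With the corrected version the order reverses: 88% for ANOVA, 86% for each alternative. The loss is at most a few points.

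**The larger disagreement figures rest on SDs wider than the plan implies.** Also true. At 4.31 days the tests almost always agree. SD 6 and 8 show sensitivity to spread and are not predictions.

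**Such detail belongs in an analysis plan.** An article may leave detail out. Here it states rules that conflict and names a model that does not fit, so the text needs correcting rather than merely expanding.

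**Conclusion.** The concern holds as a failure to fix one workable primary analysis and effect measure for length of stay. The non-fitting repeated-measures model and the two conflicting non-normal rules follow from the text without any assumption. The numerical consequence does depend on assumptions about the distribution: about 2% disagreement between tests at the plan-implied SD, rising to 10–12% at SD 6 and 18–20% at SD 8 under log-normal whole-day stays. The documents support neither a claim of inflated type I error nor one of material power loss from the gate. The correction should be made, but the point does not invalidate the trial.

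**What to change.** In Analysis of results and the abstract:

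1. Remove the K-S gate for length of stay and exclude this outcome from the repeated-measures GLM sentence.
2. Name one primary analysis, used whatever the distribution: the between-group difference in mean days from a linear model adjusted for the stratification factors in Randomization (BMI and gender), with a bootstrap or robust 95% CI. This is the scale on which the trial was sized.
3. Reconcile the ANCOVA or logistic regression sentence with this, deleting logistic regression for length of stay.
4. Name the analysis of ln(length of stay) and Mann-Whitney as sensitivity analyses.

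The cost is a few sentences, with no change to recruitment, data collection or sample size. At d = 0.8, a two-sided t-test has 90% power with 34 per arm analysed and 82% with 27. If stays are strongly skewed, the mean-difference test gives up some power to the log analysis: about 5–6 points at SD 6 and 9–10 at SD 8.

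Timing matters more than wording. Trial status says recruitment was completed on 31 December 2021, and Recruitment says the investigator knows the allocation. The choice should be made before unblinded outcome data are examined, and its date disclosed. If the data have already been examined by group, the report should say so.

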## Background

Recently, the definition of malnutrition, as proposed by the International Global Initiative on Malnutrition (GLIM), refers to a patient’s clinical condition that has at least one (1) phenotypical (involuntary weight loss, low body mass index, reduced muscle mass) or etiological criteria (reduced food intake or assimilation, inflammation, or disease burden) [1]. The levels of malnutrition severity are divided into Stage 1 (Moderate malnutrition) and Stage 2 (Severe malnutrition). This level can be determined by having one (1) phenotypic criterion that meets the grade [1].

Malnutrition is well reported in surgery patients [2, 3] especially those who have undergone major surgery [4–6], and particularly at risk in patients undergoing surgery for upper gastrointestinal or colorectal cancer [7, 8]. Preoperative malnutrition shows an increased length of hospital stay, a higher rate of surgical site infection and mortality [9], and is associated with higher postoperative complications, increased costs, poorer quality of life, and lower survival rates [9, 10]. Studies show a high prevalence of malnutrition or high nutritional risk during hospital admission [11, 12] but this is rarely assessed in the clinical setting, especially for patients who will undergo elective surgery.

The nutrition requirement for surgery is higher in comparison with the normal requirement to support a speedy recovery. Suboptimal nutritional intake will cause further depletion of the patient’s nutritional status preoperatively and a higher risk of postoperative complications. Interestingly, one of the Malaysian studies shows a significant number of post-surgery complications compared to pre-surgery which was associated with a poor level of nutrition [10].

Nutrition therapy is the provision of nutrition or nutrients either orally (regular diet, therapeutic diet, e.g., fortified food, oral nutritional supplements) or via enteral nutrition (EN) or parenteral nutrition (PN) to prevent or treat malnutrition [13] which includes dietary counseling. Nutritional therapy is important as it affects mainly the perioperative maintenance of the nutritional state to prevent postoperative complications [14]. It is strongly recommended not to wait until severe disease-related malnutrition has developed, but to start nutrition therapy early, as soon as a nutritional risk becomes apparent [15].

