**Questionnaire**				
Social demographic background	/			
The scored PG-SGA	/		/	/

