### Statistical analysis

#### Sample size calculation

A systemic review study in 2016 showed that early feeding has a significantly shorter length of hospital stay (*p*<0.01) compared to the late timing of feeding with a difference of −1.72 days and not associated with an increase in clinically relevant complications [26]. Several other studies also support early nutrition for surgery patients significantly shortening the length of hospital stay [27–29].

LOS was chosen to calculate the sample size because it has been used widely as a primary outcome in most nutrition-related RCT studies [30–32] among patients undergoing surgery. The sample size was calculated based on the data from a study conducted on colorectal cancer patients undergoing surgery [30]. The primary outcome was calculated based on the difference in LOS between two groups (control and intervention group) which was 3.45 days.

A large effect size of 0.8 for clinical significance was assumed, and practicality for this research was considered, with a power (*β*) of 90% and a probability (*α*) of 0.05. Allowing for a “drop-out” rate of 20% for the RCT study, we aim to recruit participants who will be included in each group, with the final sample size calculated as 68 participants with 34 participants in each group, respectively.

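### No primary model is named for length of stay, and the only two-group test that fits it makes no use of baseline data such as PG-SGA

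*Protocol article*

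**What the plan says.** The primary outcome is a single number per patient: "Length of hospital stay will be recorded starting from postoperative day 1 until the day of the patient’s discharge" (Length of hospital stay). Table 3 marks it at visit 2 only.

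The Analysis of results section then gives three methods:

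- An unadjusted comparison: "The values from both groups will be compared using an ANOVA test", with Kruskal-Wallis and Mann-Whitney for non-normal data. The sentence names no outcome and no covariate.
- ANCOVA or logistic regression, using "models adjusted according to potential confounders to determine predictors of changes in the key outcome variables". This is the only one of the three sentences that mentions length of stay. The confounders are not listed.
- A repeated-measures GLM for the effect of the intervention on the outcome parameters. The Abstract repeats this.

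None of the three is called primary. The same section provides for a log transformation when data are not normal.

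On baseline information, the Background states: "Preoperative malnutrition shows an increased length of hospital stay". Table 3 lists "The scored PG-SGA" at the baseline visit. Randomization is stratified by BMI and gender. The analysis text mentions neither PG-SGA nor the stratification factors as covariates.

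**The concern.** In a trial of 68 patients the choice of primary model matters, and the text leaves it open. Matching each method to the primary outcome leaves one candidate for the treatment comparison, and it is the one that uses no baseline data. The trial's own rationale is that nutritional state before surgery affects length of stay, and it measures that state in every patient before the intervention starts. A treatment comparison that sets this aside gives up precision that costs the patients nothing.

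The margin is thin. If 20% drop out as allowed for, about 27 per arm remain, and two-sided power for the unadjusted comparison is then below the stated 90%. An undesignated primary model also leaves room to choose among ANOVA, rank test and ANCOVA after the data are seen.

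**Working it through.** **Which method fits length of stay**

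| Method in the plan | Fits an outcome recorded once? | Stated as the treatment comparison? | Baseline covariates |
|---|---|---|---|
| ANOVA or rank test | Yes | Yes, for values in general | None |
| ANCOVA or logistic regression | ANCOVA does | No, stated as finding predictors | Unlisted |
| Repeated-measures GLM | No, needs at least two values per patient | Yes, for outcome parameters in general | None stated |

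Only the first row is both applicable and stated as a group comparison.

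**Inputs** (Sample size calculation)

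- Effect: "A large effect size of 0.8 for clinical significance was assumed", so d = 0.8.
- Raw difference: "difference in LOS between two groups (control and intervention group) which was 3.45 days". The implied SD is 3.45 / 0.8 = 4.31 days; the SD itself is not stated.
- Error rates: "with a power (*β*) of 90% and a probability (*α*) of 0.05", with sidedness not stated.
- Dropout 20%; 34 per arm, 68 in total.
- Correlation r between baseline PG-SGA and length of stay: **not in the documents**. Assumed 0.1 to 0.5.

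**The plan's own figure**

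n per arm = 2(z_α + z_β)² / d².

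- One-sided 0.05: 2(1.645 + 1.282)² / 0.64 = 26.8, so 27; 27 / 0.8 = 33.75, so 34 per arm and 68 in total. This matches.
- Two-sided 0.05: 2(1.960 + 1.282)² / 0.64 = 32.8, so 33 (34 by the t-test) before dropout, and 42 to 43 per arm after dividing by 0.8. This does not match.

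Power below is two-sided at 0.05, for all 34 per arm and for the 27 left after dropout (34 × 0.8 = 27.2).

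**Gain from adjustment**

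Adjusting for a covariate with correlation r multiplies the residual SD by √(1 − r²), so the effective standardised difference is 0.8 / √(1 − r²). The noncentrality is that value times √(n/2). At r = 0 this is 0.8 × √13.5 = 2.94 (27 per arm) and 0.8 × √17 = 3.30 (34 per arm). Power from the noncentral t:

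| Assumed r | Variance removed (r²) | 27 per arm | 34 per arm |
|---|---|---|---|
| 0 (unadjusted) | 0% | 82.2% | 90.2% |
| 0.1 | 1% | 82.6% | 90.4% |
| 0.2 | 4% | 83.7% | 91.3% |
| 0.3 | 9% | 85.6% | 92.6% |
| 0.4 | 16% | 88.2% | 94.4% |
| 0.5 | 25% | 91.5% | 96.3% |

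The table keeps the two-sample degrees of freedom. Estimating one covariate slope raises the variance by a factor of about 1 + 1/(2n − 4): 1/50 = 2% at 27 per arm and 1/64 = 1.6% at 34. At r = 0.1 that cancels the 1% removed, so the bottom of the range means no gain in practice.

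**Chance imbalance**

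The SD of the between-arm difference in standardised baseline PG-SGA is √(2/n): 0.272 at 27 per arm and 0.243 at 34. The probability that it exceeds 0.3 SD in either direction is 27% and 22%. At r = 0.4, a 0.3 SD imbalance moves the unadjusted difference by 0.3 × 0.4 × 4.31 = 0.52 days. The standard error of that difference is 4.31 × √(2/n) = 1.17 days (27 per arm) or 1.05 days (34), so the shift is a little under half a standard error.

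**The case against.** The strongest reply is that the plan does provide an adjusted analysis. The ANCOVA sentence is in the same paragraph, it names length of stay, and nothing keeps baseline PG-SGA out of the confounders. A reader might infer that the primary comparison ignores baseline malnutrition and that any imbalance goes uncorrected. The text does not support that: the ANOVA sentence is not labelled primary and names no outcome, and PG-SGA may enter the ANCOVA. What survives is narrower. That ANCOVA is stated as a way to find predictors, so nothing commits the trial to an adjusted treatment estimate.

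Second, a list of covariates is commonly left to the analysis plan, which is not shown. This stands, and the missing list is not the point here. The point is what the article states: an unadjusted test for the groups, ANCOVA given a different purpose, and a repeated-measures model that does not fit the primary outcome.

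Third, a reader might infer that chance imbalance biases the result. It does not. Under randomisation the unadjusted test keeps its type I error, and its standard error already allows for such imbalance.

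Fourth, BMI stratification and the entry requirement of an MST score of at least 2 limit nutritional differences to some degree. PG-SGA includes weight and an examination of fat and muscle, so it overlaps with BMI. This stands in part. PG-SGA also scores intake, symptoms, function and disease, which BMI does not balance, and an entry threshold restricts the range without balancing it between arms. The restriction could also weaken the correlation with stay, which is a reason to take the low end of the assumed range seriously.

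**Conclusion.** The concern holds as a matter of an undesignated primary model and forgone precision. It is not an error that invalidates the planned test. Three methods are named, none is primary, one cannot apply to a stay recorded once, and the only stated two-group test that fits uses no baseline information.

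The size depends on a correlation that the documents do not give. At 0.1 to 0.2 the gain in power is at most about 1.5 points with 27 per arm. At 0.3 to 0.5 it is about 3 to 9 points with 27 per arm and 2 to 6 points with 34. With 27 per arm, unadjusted two-sided power is 82.2% against the stated 90%. Adjustment would close most of that gap at a correlation of 0.4 and all of it at 0.5. The figures also assume d = 0.8, a two-sided 0.05 test, and approximate normality on the scale analysed.

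**What to change.** In Analysis of results, state that the primary treatment comparison is an ANCOVA of length of stay on randomised group, log-transformed if skewed as the section already provides. Prespecify as covariates the baseline PG-SGA score (continuous) and the stratification factors BMI and gender. Report the unadjusted ANOVA or rank test as a supporting analysis. Label the predictors model exploratory, and restrict the repeated-measures GLM to outcomes measured at more than one visit.

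The cost is a few sentences of text and a few degrees of freedom. All the covariates are collected at baseline or used for stratification, so no new data are needed. Fix the model before any outcome data are examined by group. Where that is no longer possible, report the adjusted analysis with the date on which it was specified.

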### Criteria for withdrawal

The participation will be voluntary, and the participants are free to withdraw from the study at any time any justification and this will in no way affect their future treatment.

Other possible criteria for drop-out/withdrawal are if the participant develops adverse events (AEs), suddenly has abnormal laboratory values, participants develop a condition during the study that violates the inclusion/exclusion criteria, the participant did not proceed to a qualifying operation, enteral and/or parenteral nutrition is administered after surgery, prolong fasting/nil by mouth (NBM) due to any procedure, and particular prescription from a physician that will interfere with the intervention.

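### The intention-to-treat population is given twice in consecutive sentences, once as adherers with complete data and once as everyone randomised; the two cannot both hold

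*Protocol article*

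**What the plan says.** The protocol article, Analysis of results, makes three statements that bear on this.

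- The ITT analysis makes "the assumption that participants have adhered to the dietary advice and ONS at the start of the intervention study and had baseline and endpoint values".
- The next sentence is offered as a restatement: "In other words, ITT analysis includes every randomized subject; according to randomized treatment assignment regardless of their non-compliance, subsequent withdrawal from treatment". It goes on to cover protocol deviations and later events as well.
- Treatment effects on the outcome parameters are then assigned to one method: "The effect of intervention between treatment groups on outcome parameters will be carried out by using General Linear Model (GLM) for repeated measure procedure". The abstract names the software: outcomes "will be analyzed by using the SPSS General Linear Model (GLM) for the repeated measure procedure".

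Two other sections matter. Under Length of hospital stay, the primary outcome is a single value: "The total length of hospital stay will be taken during visit 2, the day of the patient’s discharge". Criteria for withdrawal lists events after randomisation that may end participation, among them "the participant did not proceed to a qualifying operation, enteral and/or parenteral nutrition is administered after surgery, prolong fasting/nil by mouth (NBM) due to any" (this quote stops one word short of the end of the item), along with adverse events and abnormal laboratory values.

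**The concern.** The two ITT sentences are joined as if they said the same thing, but they describe different sets of patients. The first conditions on behaviour and data availability after randomisation, which is what an ITT analysis is meant to avoid. If it is followed, the groups compared are no longer those created by randomisation, yet the result carries the ITT label.

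The primary comparison is exposed because the condition can remove patients whose LOS is already in the hospital record. Several listed withdrawal reasons describe a difficult postoperative course, which may well be related to LOS. The choice of set therefore need not be neutral for the primary outcome.

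There is a smaller, separate issue for the repeatedly measured secondary outcomes. The named procedure works on complete cases, so even an analyst who follows the second sentence would not obtain every randomised participant from it.

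**Working it through.** The protocol attaches no figure to this point, so the check sets the passages side by side.

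**Step 1. Who is in the analysis under each sentence?**

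| Participant | LOS known? | First sentence | Second sentence |
|---|---|---|---|
| SS, operated on, did not take the supplement as prescribed at the start | Yes | Out | In |
| Either arm, operated on, did not follow the dietary advice at the start | Yes | Out | In |
| Either arm, discharged, no visit 3 | Yes | Out if the endpoint is taken as visit 3 | In |
| Either arm, operated on, then meets a withdrawal criterion | Yes, from the hospital record | Out if withdrawal leaves no endpoint value | In |
| Either arm, never operated on | No postoperative LOS exists | Out | In, but without an LOS value |

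The sentences disagree in every row, two of them conditionally. In the first four rows LOS can be obtained.

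**Step 2. Does the condition act equally on the arms?** Table 2 (ONS allocation) gives supplements to SS only, so only an SS patient can fail that part. Dietary advice goes to both arms (Control group, Group NN; Data collection procedure), and both arms can lack data. The condition as a whole is therefore not confined to one arm, but one component is.

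**Step 3. Does the data condition fit the primary outcome?** LOS counts from postoperative day 1 and is taken once, at discharge. It has no baseline value, so that half of the condition is empty. The word endpoint is open: Data collection procedure places the end of the study at visit 3, about 4 weeks after discharge. On that reading, a patient with a recorded LOS could be excluded for a missed later visit.

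**Step 4. How large could the effect on LOS be?** The documents do not say how many patients the clause would exclude or how their stays differ. Purely as an illustration with assumed inputs, suppose a share f of one arm is removed and those removed stay x days longer than those kept. The mean of the kept patients then differs from the full-arm mean by f × x:

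- f = 0.10, x = 3: 0.10 × 3 = 0.3 days
- f = 0.20, x = 5: 0.20 × 5 = 1.0 day
- f = 0.30, x = 5: 0.30 × 5 = 1.5 days

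Against the 3.45-day difference in Sample size calculation, the ends of this range are 0.3/3.45 = 9% and 1.5/3.45 = 43%. The sign reverses if those removed stay less long, and similar removals from the other arm would offset it.

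**Step 5. What does the repeated-measures procedure do?** SPSS GLM repeated measures drops any case missing one of the modelled visits, unless values are imputed first. This is a property of the procedure, not protocol text.

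- Table 3 schedules handgrip at all four visits. PG-SGA, weight, arm circumference, skinfold and dietary intake are taken at baseline and two later visits. A patient missing one visit contributes nothing to that outcome's model.
- Biochemistry is taken at baseline and visit 3 only. A patient missing visit 3 has no post-baseline value, and no choice of model recovers one.
- LOS is a single value, so the procedure does not apply to it.

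**The case against.** The strongest reply is that the first sentence states an assumption, not an inclusion rule, and that the second says plainly who is included. On that reading the text is clumsy and the intention is ITT. Part of this stands: the second sentence is the clearer of the two, and it is the one to keep. But whether a patient adhered or has an endpoint value is a fact about that patient. Where the assumption fails, it can be made true only by leaving the patient out.

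It can also be said that missing-data handling commonly belongs in the analysis plan, which is not shown. That is fair. It limits the repeated-measures point to a conditional remark on secondary outcomes, and that procedure would in any case enforce only the complete-data condition, not adherence. It does not remove a contradiction printed in the protocol itself.

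Three stronger readings are tempting but unsupported:

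- **Selection acts on the intervention arm alone.** Controls also receive advice and can also lack data; only the supplement component is one-sided.
- **About 14 of 68 patients would be excluded.** That is 0.20 × 68 = 13.6, the planned drop-out allowance. It is not a count of those failing the clause, and it may mix non-adherers, patients never operated on and losses after discharge.
- **Missing visit 3 biases LOS in favour of the intervention.** LOS is already known at discharge, and nothing in the protocol makes later losses heavier in SS.

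**Conclusion.** The contradiction is explicit and should be corrected: the population for the primary comparison is stated in two incompatible ways, and one of them is not ITT. It could exclude patients with a known LOS. Bias is possible, but its size and direction are not established. The 0.3 to 1.5 days above rests wholly on assumed inputs and shows only that the effect need not be negligible beside 3.45 days.

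The repeated-measures point is secondary. It holds for handgrip, PG-SGA, anthropometry and dietary intake, provided no imputation is specified elsewhere. It concerns neither LOS nor adherence.

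**What to change.** 1. Delete the clause on adherence and on having values at both ends. Define ITT as all randomised participants in their allocated group.
2. For LOS, use the hospital record for every randomised participant who has surgery, whatever their supplement intake or later attendance. Include those who meet a withdrawal criterion after surgery, subject to consent for use of the record. State that withdrawal under those criteria does not remove a participant from the LOS analysis.
3. Report by arm, with reasons, those never operated on. They have no postoperative LOS, so the LOS analysis falls short of all randomised by that number, and the article should say so.
4. Label any adherer or completer analysis per-protocol and treat it as supportive.
5. For secondary outcomes with more than one post-baseline visit, use a linear mixed model (SPSS MIXED: group, visit, group by visit, baseline value as covariate) on all available visits. Imputation before the GLM is an alternative. For biochemistry, report the number with a visit 3 value in each arm.

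The cost is mainly wording. LOS is already to be collected, and the mixed model is in the same software. It requires data missing at random, a weaker assumption than complete cases generally need. It recovers nothing for patients with no post-baseline value.
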